## Abstract

**Background::**

Transient receptor potential vanilloid 2 (TRPV2) was previously shown to play an important role in the maintenance of cancer stem cells, and its specific inhibitor, tranilast, also has potential as a targeted therapeutic agent for esophageal squamous cell carcinoma (ESCC). The present study is being conducted to confirm the safety and efficacy of the additional use of tranilast with conventional preoperative adjuvant chemotherapy for patients with advanced ESCC.

**Patients and methods::**

Between 56 and 59 patients aged between 20 and 74 years with clinically diagnosed Stage II or Stage III ESCC will be enrolled. Eligible patients will receive preoperative adjuvant chemotherapy, 2 cycles of combination therapy with cisplatin, 5-fluorouracil, and tranilast. Recruitment started in November 2019, with the final follow-up being planned for March 2029. One subject has been enrolled since October 21^st^, 2020. The pathological therapeutic effect is the primary endpoint. The objective response rate, safety of preoperative adjuvant chemotherapy, recurrence-free survival (RFS), and overall survival (OS) are the secondary endpoints. RFS and OS will be calculated as the time from surgery to first recurrence and all-cause death, respectively.

**Ethics and dissemination::**

This protocol has been approved by the Institutional Review Boards of Kyoto Prefectural University of Medicine and all participating hospitals in August 30, 2019 (Number: CRB5180001). Written informed consent will be obtained from all patients before their registration, which is in accordance with the Declaration of Helsinki. The results of the present study will be disseminated via publication in peer-reviewed journals.

**Trial registration::**

Trial registration number jRCTs051190076

## Introduction

1

The outcome of esophageal squamous cell carcinoma (ESCC), an aggressive type of neoplasm, has recently been improved in Japan due to advances in multidisciplinary treatments that combine surgery, chemotherapy, and radiotherapy.^[1–3]^ ESCC is a major cause of cancer-related death worldwide, and it frequently recurs in patients with advanced disease, whose prognosis remains poor.^[1–5]^

Despite multidisciplinary treatments, ESCC cells may acquire treatment resistance, persist, and ultimately cause recurrence. Previous studies reported that a large number of solid tumors include a minor subset of cancer cells called cancer stem cells (CSCs).^[6,7]^ These cells have the characteristics of stem cells, such as self-replication ability and pluripotency, exhibit resistance to anticancer drugs and radiation, and are critically involved in tumor initiation, progression, recurrence, and metastasis, ultimately resulting in patient death.^[6,7]^ We previously demonstrated that the expression levels of transient receptor potential vanilloid 2 (TRPV2), a nonspecific cation channel, were very high in the CSCs of ESCC.^[7]^ The cytotoxicity of tranilast, an analog of a tryptophan metabolite and a TRPV2 inhibitor, was shown to be more potent at a lower concentration in CSCs than in non-CSCs.^[7]^ It has been used to treat patients with inflammatory diseases, such as asthma, dermatitis, allergic conjunctivitis, keloids, and hypertrophic scars.^[8]^ The safety of tranilast for clinical use has already been demonstrated.^[9]^

Preoperative adjuvant chemotherapy with cisplatin (CDDP) and 5-fluorouracil (5FU) is currently used with beneficial effects to treat localized advanced ESCC in Japan.^[2,3,10]^ We previously reported that TRPV2 appeared to play a role in maintaining CSCs, and that tranilast, its inhibitor, may enhance the effects of conventional preoperative adjuvant chemotherapy against ESCC.^[7]^ The present study is being performed to confirm the safety and efficacy of the additional use of tranilast with 5-FU/CDDP and to develop a novel therapeutic strategy for patients with advanced ESCC.

## Materials and methods

2

### Study design

2.1

The present study is a single arm, open-label prospective intervention phase I/II trial.

### Objectives

2.2

The purpose of the present study is to confirm the clinical safety and efficacy of the additional use of tranilast with conventional preoperative adjuvant chemotherapy (5-FU/CDDP) for patients with advanced ESCC in a phase I/II design.

### Study setting

2.3

The study is an investigator-initiated, prospective intervention phase I/II trial to investigate the efficacy of the additional use of tranilast using comparisons with historical control data from patients who previously received conventional preoperative adjuvant chemotherapy (5-FU/CDDP) in our institute. Patients will provide written informed consent before their registration, which is in accordance with the Declaration of Helsinki. Following an independent review by the Center for Quality Assurance in Research and Development, Kyoto Prefectural University of Medicine, patients will be registered in the present study. In accordance with the Japanese clinical trial guidelines, at least annual independent monitoring is planned.

### Participants

2.4

Patients clinically diagnosed with Stage II or Stage III ESCC and indicated for esophagectomy after preoperative adjuvant chemotherapy will be recruited. The following inclusion criteria are being used:

1.Histologically proven ESCC.2.Clinically diagnosed Stage II or Stage III ESCC staged according to the 11^th^ edition of the Japanese Classification of Esophageal Cancer.^[11,12]^3.Patients considered eligible for radical esophagectomy under general anesthesia.4.Aged between 20 and 74 years at the time of enrollment.5.Patients with ECOG performance status 0, 1, or 2.6.Confirmed adequate organ functions within 14 days before enrollment. The following clinical test standards were used:a.Creatine ≤1.2 mg/dLb.Blood urea nitrogen ≤25 mg/dLc.Creatinine clearance ≥60 mL/mind.Total bilirubin ≤1.2 mg/dLe.Glutamic oxaloacetic transaminase, glutamic pyruvic transaminase ≤twice the upper limit of the institutional reference valuef.White blood cell count ≥4000 cells/mm^3^g.Hemoglobin ≥8.0 g/dLh.Platelet count ≥100,000 cells/mm^3^i.PaO_2_ ≥70 torr7.Patients who can take medicine.8.Oral and written informed consent obtained before registration.

The following exclusion criteria are being applied:

1)History of chemotherapy, radiation, or administration of other investigational agents for synchronous or metachronous malignancies within 1 year before enrollment.2)Tumor with active bleeding.3)A patient with a history of acute myocardial infarction, severe angina, congested heart failure, cerebrovascular disease, or pulmonary thrombosis within 6 months before registration.4)Uncontrollable asthma.5)History of laparotomy or thoracotomy within 4 weeks before treatment begins.6)Allergy to tranilast.7)Females who may be pregnant, breastfeeding an infant, and have a desire to bear children.8)Any other patients considered to be unsuitable for enrollment by the investigators.9)A patient who takes some similar drugs to tranilast.10)A patient who received a transfusion within 14 days before enrollment.11)Currently being medicated with warfarin.

### Dose and treatment regimens of preoperative adjuvant chemotherapy

2.5

Preoperative adjuvant chemotherapy will comprise 2 cycles of combination therapy with 80 mg/m^2^ CDDP on day 1, 800 mg/m^2^ 5-FU on days 1 to 5, and 200 to 600 mg/day tranilast on days 1 to 21 every 3 weeks (Table 1).

**Table 1 T1:** Protocol treatment schedule for preoperative adjuvant chemotherapy (1 cycle).

Drug	Dose	Administration method	Administration day
CDDP	80 mg/m^2^	Intravenous drip	Day 1
5-FU	800 mg/m^2^	Intravenous drip	Days 1–5
Tranilast	200–600 mg/body	Oral administration	Days 1-21

5-FU = 5-fluorouracil; CDDP = cisplatin.

Toxicities will be assessed based on the Common Terminology Criteria for Adverse Events (CTCAE) version 5.0. Dose-limiting toxicity (DLT) will be defined by the occurrence of severe toxicities, CTCAE grade 4 or 5. The CTCAE grade 4 adverse reactions which often occur during CDDP and 5FU therapy, such as neutropenia, thrombocytopenia, stomatitis, and diarrhea, will be excluded from DLT.

To identify the maximum tolerated dose (MTD) of tranilast, 200 mg/day tranilast will be administered to the first 3 patients. If 2 cycles of combination therapy are successively completed without DLT, 300 mg/day tranilast will be administered to the next 3 patients. The dose of tranilast will gradually be increased to 600 mg/day, and the appropriate MTD will be established (Fig. 1). This clinical study will be stopped when DLT occurs at 200 mg/day tranilast (Fig. 1). Dose modifications will be permitted when DLT occurs at 300 or 600 mg/day tranilast (Fig. 1).

**Figure 1 F1:**
[figure not shown]
Establishing the maximum tolerated dose (MTD) of tranilast. Initially, 200 mg/day tranilast will be administered to the first 3 patients. If 2 cycles of combination therapy are successfully completed without dose-limiting toxicity (DLT), 300 mg/day tranilast will be administered to the next 3 patients. The dose of tranilast will gradually be increased up to 600 mg/day, and the appropriate MTD will be established. This study will be stopped when DLT occurs at 200 mg/day tranilast. Dose modifications are allowed when DLT occurs at 300 or 600 mg/day tranilast. DLT: grade 4 toxicity according to the Common Terminology Criteria for Adverse Events (CTCAE) version 5.0.

Two cycles of combination therapy with the established MTD of tranilast will then be given to 50 patients. Their data will be compared with historical control data from patients who previously received conventional preoperative adjuvant chemotherapy (5-FU/CDDP) in our institute. This clinical study will be stopped when grade 4 toxicity occurs at the MTD of tranilast in >5 patients.

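### DLT is defined differently in the section 2.5 text and the Figure 1 legend, and the phase II stopping rule does not say whether expected backbone toxicity or grade 5 counts

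*Protocol article*

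**What the plan says.** The Protocol article states the toxicity criterion in three places.

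- **Section 2.5, main text.** "Dose-limiting toxicity (DLT) will be defined by the occurrence of severe toxicities, CTCAE grade 4 or 5". The next sentence removes grade 4 reactions that are frequent under CDDP and 5-FU, "such as neutropenia, thrombocytopenia, stomatitis, and diarrhea, will be excluded from DLT". The four reactions are given as examples.
- **Figure 1 legend.** "DLT: grade 4 toxicity according to the Common Terminology Criteria for Adverse Events (CTCAE) version 5.0". It has no exclusion and does not mention grade 5.
- **Phase II rule, in the paragraph after the legend.** "This clinical study will be stopped when grade 4 toxicity occurs at the MTD of tranilast in >5 patients". It does not use the term DLT, has no exclusion and does not mention grade 5.

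Decisions hang on these statements. At the first dose level, "200 mg/day tranilast will be administered to the first 3 patients", and section 2.5 ends the whole study if a DLT occurs at that level. Escalation to 300 mg/day requires two cycles without DLT, and a DLT at 300 or 600 mg/day permits dose modification. The dose so established is carried into phase II: "Two cycles of combination therapy with the established MTD of tranilast will then be given to 50 patients". Nothing in the article says that the exclusion in the text carries over to the legend or to the phase II rule.

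**The concern.** One term has two definitions, and a study-ending action is attached to it. A single isolated grade 4 neutropenia at 200 mg/day does not count under the section 2.5 text but stops the trial under the legend. A grade 5 event is a DLT under the text and, read literally, is not one under the legend. The legend cannot simply be set aside, because section 2.5 refers to Figure 1 three times for the escalation and stopping steps.

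In phase II the problem is one of silence. As worded, the rule counts grade 4 events that the protocol itself attributes to the backbone. Enough of these could stop the trial even if tranilast added no toxicity. The rule also leaves open whether a grade 5 event adds to the count. If the team meant the phase II rule to use a different set of events from DLT, the document does not say so.

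**Working it through.** **Step 1: set the statements side by side.**

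| Statement | Grade 4, expected with CDDP/5-FU | Grade 4, other | Grade 5 |
|---|---|---|---|
| Section 2.5 text (DLT) | excluded | counts | counts |
| Figure 1 legend (DLT) | counts | counts | not mentioned |
| Phase II rule | counts | counts | not mentioned |

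There are three statements but two literal sets of events, because the legend and the phase II rule share the same unqualified wording. Rows 1 and 2 define the same term and disagree in two of three columns; that is the direct contradiction. Row 3 is a separate rule whose relation to row 1 is not stated.

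**Step 2: how much the list of events could matter.** The plan states no stopping probability for either rule, so there is no figure of its own to reproduce. The sample size of 48 in section 2.6 does not enter this point.

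Inputs from the documents:
- first cohort of 3 patients, with the study stopped by any DLT at 200 mg/day (section 2.5)
- 50 phase II patients, with a stop at more than 5, that is 6 or more (paragraph after the Figure 1 legend)

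Input that is assumed: the per-patient probability *p* of a counted event, since the documents give no grade 4 rate. Patients are taken as independent with a common *p*, and tranilast is taken to add nothing.

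Formulas:
- Phase II: P(X ≥ 6) = 1 − Σ(k = 0 to 5) C(50, k) p^k (1 − p)^(50−k)
- First cohort: P(at least 1 of 3) = 1 − (1 − p)^3; for example, at p = 0.10, 1 − 0.9^3 = 1 − 0.729 = 0.271

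| Assumed p | P(>5 of 50) | P(at least 1 of 3) |
|---|---|---|
| 2% | <0.1% | 5.9% |
| 5% | 3.8% | 14.3% |
| 10% | 38.4% | 27.1% |
| 15% | 78.1% | 38.6% |
| 20% | 95.2% | 48.8% |

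The low rows illustrate a list on which few events count, and the high rows a list on which all grade 4 events count.

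**Step 3: sensitivity to the denominator.** Section 2.6 takes 3 of the 50 phase II patients from phase I at the established dose. If those 3 are assumed to have had no counted event, the rule needs 6 or more among 47 new patients. The probabilities at 5, 10, 15 and 20% are then 2.9, 32.9, 72.7 and 93.0%. The picture does not change.

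**The case against.** The strongest reply is that the legend is shorthand. The section 2.5 text is the operative definition and gives its exclusion explicitly. The legend line is a closing gloss on an abbreviation, in an article that condenses a longer protocol, and the figure itself is not available here. An investigator who has read the text may well not stop the trial over a caption. This is plausible, but the document does not say that the text prevails, and a stopping rule should not depend on a guess.

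A second reply is that a cumulative phase II tolerance rule may properly count different events from a 3-patient escalation rule. That is right. The difference between the phase II rule and DLT is therefore not in itself an error; what is missing is a statement that it is intended.

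Two stronger readings are tempting and are not supported:

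- A reader might infer three incompatible definitions. There are two sets of events, and only the text and the legend conflict over one term.
- A reader might infer that deaths are disregarded in phase II. The rule only fails to mention grade 5. The section 2.5 text names grade 5 as a DLT, section 2.9 requires immediate reporting of adverse events to the principal researcher, section 2.8 places the trial under Ethics Committee supervision, and section 2.3 plans independent monitoring at least once a year. None of these supplies a numerical rule for grade 5, but they do not suggest that a death would pass without action.

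Finally, the probabilities rest wholly on assumed rates. They show that the choice of events can matter, not that the trial is likely to stop. An article may also leave operating characteristics to the full protocol.

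**Conclusion.** The point holds as an internal contradiction in the DLT definition, together with an incompletely specified phase II stopping rule. The contradiction needs no assumption: it can be read directly from the section 2.5 text and the Figure 1 legend, and it bears on the stop at 200 mg/day, on escalation and hence on the dose taken into phase II. The effect on the eventual MTD has not been quantified.

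The phase II rule as worded could be met by backbone toxicity alone. How likely that is cannot be known from the documents. Over assumed background rates of 5 to 20% the chance runs from about 4% to about 95%, and under the legend the chance of a stop in the first cohort of 3 runs from about 14% to about 49%. The primary endpoint, the 19% and 34% rates and the sample size are not affected. Because the wording governs safety decisions and is cheap to repair, it should be corrected.

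**What to change.** - Reconcile the section 2.5 text and the Figure 1 legend to a single DLT definition, with the same grades and the same exclusions in both places.
- In the phase II rule, state which grades and exclusions apply and how a grade 5 event is handled. If the counted events are meant to differ from DLT, say so.

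Which events should count is a decision for the clinical team, and no view is taken here. The cost is a wording change in three places, with approval of the revised protocol as section 2.8 requires.

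Optionally, the team could compute the chance of stopping under each rule at the grade 4 rate in the institute's own CDDP/5-FU historical series, if that series recorded toxicity. This is one small table. It would be useful, but its absence from the article is not an error.

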### Rationale for setting the target population size

2.6

Between 56 and 59 patients will be enrolled in the present study. An analysis of historical control data from patients who previously received conventional preoperative adjuvant chemotherapy (5-FU/CDDP) in our institute showed good pathological therapeutic effects (tumor regression grade 2 or 3 according to the 11^th^ edition of the Japanese Classification of Esophageal Cancer^[11,12]^) in 19% of patients. Therefore, expected and threshold rates are 34% and 19%, respectively. Under these conditions, 48 subjects will be required based on the assumption of a 1-sided alpha error of 0.05 and beta error of 0.2. In consideration of dropouts, the sample size is set at 50 patients for the phase II trial. Between 9 and 15 patients will be required to establish MTD (phase I trial). Data from 3 of these patients with established MTD will be used for the phase II trial. Therefore, the total sample size has been set at 56 to 59 patients in the present trial.

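### The stated total of 56 to 59 patients does not follow from its own components at the upper end: 15 + 50 - 3 gives 62, not 59

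*Protocol article*

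**What the plan says.** The components and the total all stand in section 2.6 (Rationale for setting the target population size).

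- Phase I: "Between 9 and 15 patients will be required to establish MTD (phase I trial").
- Phase II: "In consideration of dropouts, the sample size is set at 50 patients for the phase II trial". This rounds up a calculated requirement of 48.
- Overlap: "Data from 3 of these patients with established MTD will be used for the phase II trial". The overlap is a single number, not a range.
- Total: "Therefore, the total sample size has been set at 56 to 59 patients in the present trial". The opening word presents the total as the result of the preceding figures.

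The same range opens section 2.6 and appears in the abstract: "Between 56 and 59 patients aged between 20 and 74 years with clinically diagnosed Stage II or Stage III ESCC will be enrolled".

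The text of section 2.5 that follows Figure 1 describes phase II as: "Two cycles of combination therapy with the established MTD of tranilast will then be given to 50 patients". It does not say whether the 50 include the phase I patients who are carried over.

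**The concern.** A reader who adds the three components gets the stated minimum but not the stated maximum. A phase I range that is 6 wide (9 to 15), combined with a fixed phase II size and a fixed overlap, must give a total range that is 6 wide. The stated range is 3 wide, so at least one of the figures 15, 3 and 59 cannot be right as written.

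What is at stake is mainly clarity about enrolment. Those running the trial need to know how many patients may be recruited, and how many of the 50 in the primary analysis come from phase I. If the total were applied as a ceiling while the other figures also held, phase II could fall slightly short of its own requirement.

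**Working it through.** **Inputs, all from section 2.6.** Phase I: 9 to 15. Phase II: 50. Shared: 3. For the power check: "expected and threshold rates are 34% and 19%, respectively", 1-sided alpha 0.05, beta 0.2, required n = 48.

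**Step 1: the total.** Total = phase I + phase II - shared.

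- Lower end: 9 + 50 - 3 = 56. This reproduces the stated minimum.
- Upper end: 15 + 50 - 3 = 62. The stated maximum is 59, a gap of 3 (3/59 = about 5%).

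**Step 2: what would give 59?** With 50 in phase II:

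| Phase I | 0 shared | 3 shared | 6 shared |
|---|---|---|---|
| 9 | 59 | 56 | 53 |
| 12 | 62 | 59 | 56 |
| 15 | 65 | 62 | 59 |

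As a maximum, 59 fits either a phase I maximum of 12 with 3 shared, or a phase I maximum of 15 with 6 shared. The remaining cell, 9 with none shared, uses the phase I minimum and drops the overlap. Every cell that gives 59 changes a stated figure. Replacing 50 by the calculated 48 does not help: 9 + 48 - 3 = 54 and 15 + 48 - 3 = 60.

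**Step 3: is the phase II figure the source?** The one-sample normal approximation, with null variance for alpha and alternative variance for power, is

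n = [(1.645 × √(0.19 × 0.81) + 0.842 × √(0.34 × 0.66)) / 0.15]² = 48.4.

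This agrees with the stated 48 to within rounding. The phase II size is not where the gap arises.

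**Step 4: the conditional consequence.** Suppose that phase I uses 15 patients, 3 are carried over, and enrolment stops at 59. Patients treated at the MTD then number 59 - 15 + 3 = 47, against 50 planned and 48 required.

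Power by the same approximation is Φ[(0.15√n - 1.645 × √(0.19 × 0.81)) / √(0.34 × 0.66)]:

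- n = 50: Φ(0.877) = 81.0%
- n = 47: Φ(0.809) = 79.1%

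The loss is about 2 percentage points.

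**The case against.** The strongest reply is that 59 may well be right and the overlap of 3 merely loose wording. Suppose the first dose level takes 3 patients, each of the next two takes 3 or 6, and everyone treated at the MTD is carried over. Phase I is then 9 to 15 and the total is always 56 or 59. That would explain the stated range fully, and Figure 1, which is not available here, might show such a scheme. But this is an assumption. The text describes cohorts of 3 (for the first level, "200 mg/day tranilast will be administered to the first 3 patients"), mentions no expansion to 6, and fixes the overlap at 3. The reply therefore stands as a reason not to declare 62 correct. It does not make the written sum work.

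Three stronger readings are tempting, and the documents do not support them.

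- *A large loss of power.* Exact binomial power is 67.1% at n = 47 (cut-off 15, alpha 2.4%) and 77.0% at n = 50 (cut-off 15, alpha 4.1%), so a reader might infer a 10-point loss. Most of that is discreteness: n = 46 gives 74.4% (cut-off 14, alpha 4.2%), more than n = 47. Section 2.6 names no exact test, and the approximation that reproduces its 48 shows a loss of about 2 points. Nor does any passage say that 59 would override the stated phase II size of 50.
- *Fifty new patients after phase I.* Read alone, section 2.5 could mean a total of 59 to 65. Section 2.6 answers this by counting phase I patients toward phase II. Section 2.5 is unclear, not contradictory.
- *Selective choice of 3 out of 6 MTD patients.* This bias would require a cohort of 6 at the MTD, which the text does not describe. Nothing indicates a selection made with outcomes known.

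**Conclusion.** The inconsistency is real and rests only on figures within section 2.6: the components give 56 to 62, and the article states 56 to 59. It amounts to 3 patients, about 5%, at the upper end only. The lower end, the hypotheses, the alpha level and the planned phase II size of 50 are untouched.

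Which of 15, 3 and 59 is wrong cannot be settled from the documents. The shortfall to 47 patients depends on three conditions holding together: a 15-patient phase I, exactly 3 carried over, and 59 enforced as a ceiling ahead of the 50. Even then the cost is small, although it would use up the dropout allowance and fall 1 patient below the stated 48. Those 47 would be patients treated at the MTD, and any dropouts would come off that number. Severity: minor to moderate. It should be corrected because a stated sample size fails its own sum, not because power or bias is shown to be at risk.

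**What to change.** Reconcile the three figures in section 2.6 and carry the result into the abstract. Depending on what the sponsor's phase I scheme allows, one of the following would do:

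1. State that all phase I patients treated at the declared MTD count toward the 50. If that number can be 3 or 6, the range stands: 9 + 50 - 3 = 56 to 15 + 50 - 6 = 59.
2. If 3 is always the overlap and phase I cannot exceed 12, correct the phase I maximum to 12: 12 + 50 - 3 = 59.
3. If 15 and 3 are both right, restate the maximum total as 62.

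In section 2.5, add that the 50 patients include those carried over from phase I.

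The cost is a few words in sections 2.5 and 2.6, plus the abstract if the range changes. Options 1 and 2 keep the stated total. Option 3 raises the stated maximum by 3 patients. Section 2.8 requires renewed committee approval for protocol modifications, so if the full protocol carries the same figures, the correction should go through that route. The article reports only one subject enrolled, so the change would come early in recruitment.
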